### Outcomes

The primary objective is to evaluate whether treatment with high-dose LMWH in patients with coiled aSAH significantly reduces mortality assessed at 30 days after the initial bleeding. Secondary objectives are to evaluate whether this treatment significantly reduces the presence and severity of DCI (measured by the Modified National Institutes of Health Stroke Scale),^29^ increases the incidence of major bleeding (defined as a fatal bleeding and/or symptomatic bleeding in critical areas or organs (such as intracranial, intraspinal, intraocular, retroperitoneal, intra-articular, pericardial or intramuscular bleeding causing compartment syndrome) and/or bleeding resulting in a haemoglobin drop of 1.2 mmol/L or more, or requiring a transfusion of two or more units of whole blood or red cells) and non-major bleeding (defined as all reported bleedings not classified as major),^30^ increases the risk of haemorrhagic complications after shunt placement or lumbar puncture, reduces other SAH-related complications (such as severe hyponatraemia, postprocedural aneurysm rupture, rebleeding, delirium, epilepsy, diffuse parenchymal swelling or nosocomial infections), reduces the incidence of shunt-dependent hydrocephalus, increases the rate of discharge to home, improves quality of life at 6 months, enhances cognitive functioning at 6 months, increases the likelihood of a favourable outcome at 6 months and reduces mortality at 6 months. Outcome assessments are done by a trial nurse at the outpatient clinic 6 months after the initial bleeding, with the standard follow-up performed on the same day. The trial nurse is blinded for group allocation and does not participate in the medical treatment of the included patients. In addition, peak anti-Xa levels are measured at 12:00 on day 7 following the ictus and are readily available for analysis. A comprehensive panel of coagulation and inflammatory biomarkers is also being collected and will be analysed after completion of patient inclusion. The biomarkers include von Willebrand factor, syndecan-1, soluble thrombomodulin, tumour necrosis factor-alpha, interleukin (IL)-6, IL-8, soluble vascular cell adhesion molecule-1, angiopoietin, a disintegrin and metalloproteinase with thrombospondin motifs 13, D-dimer and coagulation factor III (also known as tissue factor). All biomarker measurements are performed on day 7 following the ictus.

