Nadroparin was selected as the investigational product over other LMWHs or UFH based on both practical and theoretical considerations. In our institution, therapeutic use of UFH requires intensive monitoring and titration, which can only be performed in the intensive care unit (ICU) setting. This would necessitate prolonged ICU admission—up to 3 weeks—for all study participants, making it logistically and ethically unfeasible. Furthermore, achieving stable anticoagulant levels with UFH is notoriously difficult in critically ill patients, with the activated partial thromboplastin time often failing to accurately reflect heparin activity, thus increasing the risk of both underdosing and overdosing.^26 27^ Nadroparin, by contrast, has a more predictable pharmacokinetic profile, can be administered subcutaneously and allows for reliable monitoring via anti-Xa levels. Additionally, the potential non-anticoagulant, pleiotropic effects of heparins—such as modulation of neuroinflammation and apoptosis—are expected to be shared across both UFH and LMWHs.^22^ Thus, nadroparin was chosen as the most suitable agent to evaluate the therapeutic potential of heparins in this vulnerable patient population. We hypothesise that treatment with high-dose nadroparin significantly reduces 30-day mortality compared with standard care. To determine this potential benefit, we will conduct an RCT titled ‘Improving outcome in SubaraChnoid HEMorrhage wIth nAdroparin’ (ISCHEMIA). The ISCHEMIA trial challenges existing treatment paradigms, which are mostly aimed at blood-induced vasospasm and will be the first RCT to investigate the effect of high-dose LMWH in patients with aSAH.

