### Interventions

Patients in the intervention group will receive a high dose of LMWH, specifically nadroparin 5700 AxaIU administered two times per day. Treatment will start as soon as the redeemed safe is available, but no later than 24–72 hours after coiling and will continue for 21 days following the initial SAH. For safety reasons, high-dose nadroparin will only be administered to patients with a secured aneurysm. The current inclusion criteria consider both the time of ictus and the timing of coiling. Only patients who undergo coiling within 72 hours of ictus are eligible for inclusion, with most starting nadroparin within 24 hours after coiling. In clinical practice, the majority of eligible patients present on the day of ictus or the following day and are coiled within 24 hours. Since DCI typically develops between days 4 and 10 after SAH, this time frame is considered an appropriate therapeutic window. If discharged home before 21 days, the treatment will stop on discharge. If hospitalisation extends beyond 21 days, the prophylactic dose will be continued until discharge or until the patient is mobilised for more than 6 hours per day. The high dose of nadroparin used in this study is solely considered therapeutic in patients weighing under 70 kg. This fixed dosing approach reflects the study’s focus not solely on anticoagulant effects but also on the broader pleiotropic properties of LMWH, such as anti-inflammatory and endothelial-stabilising actions. In general, target anti-Xa levels for nadroparin are unknown. Based on observed anti-Xa levels in subjects with a therapeutic weight-based dose, reference ranges are regularly around 0.6–1.2 IU/mL. However, it remains uncertain whether benefits and harms of nadroparin are optimally maintained in this range.^28^

In the control group, patients will receive standard care with a prophylactic dose of LMWH (nadroparin; 2850 AxaIU once daily for those weighing ≤100 kg, or 5700 AxaIU once daily for those weighing >100 kg), starting within 24 hours after coiling and continuing until discharge or when mobilised for at least 6 hours daily.

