This trial has some limitations. As a phase II RCT with a small sample size, it lacks the power to provide definitive conclusions about the effect of high-dose nadroparin on mortality and other parameters, necessitating a larger phase III RCT for confirmation. The trial is not fully blinded. We opted for an open-label approach due to both practical and ethical considerations. Nadroparin carries a risk of bleeding, and early recognition of haemorrhagic complications is essential. Unblinding in response to clinical deterioration may delay critical decisions or lead to uncertainty in management. Moreover, the dosing regimens differ between groups: patients in the intervention group receive nadroparin two times per day, while those in the control group receive it once daily. This distinction makes full blinding unfeasible, as it would likely be apparent to both patients and care providers. Additionally, nadroparin has measurable pharmacodynamic effects—such as anti-Xa levels—which would further compromise blinding, as clinicians could infer treatment allocation from laboratory results. Using a placebo control with sham anti-Xa monitoring was considered but deemed both ethically and logistically challenging. Simulating treatment would require drawing blood and performing lab tests solely to maintain blinding, offering no clinical benefit and exposing critically ill patients to unnecessary procedures. To minimise bias, a blinded trial nurse was included, and the primary outcome—mortality—was selected for its objectivity and resistance to observer bias. A further limitation of the study is that not all patients may complete all dosages due to emergency interventions requiring temporary cessation of the study medication, such as lumbar punctures or ventricular catheter placements. The heterogeneity of aSAH patients and the exclusion of those with intraparenchymal haemorrhage or non-endovascular treatments complicate the generalisation of results to the broader aSAH population or to settings preferring different aneurysm occlusion methods, such as clipping. Preferably, a larger and more diverse population will be included in future trials to establish broader applicability, if deemed safe.

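### Non-major bleeding pools every reported bleed below major in an open-label comparison of two daily injections with one, so an excess could not be read as systemic or clinically relevant bleeding

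*Protocol article*

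**What the plan says.** Under Outcomes, the protocol article lists as a secondary objective whether high-dose treatment increases major and non-major bleeding. Major bleeding has its own criteria: death, critical site, haemoglobin drop or transfusion. Everything else falls into one class: "non-major bleeding (defined as all reported bleedings not classified as major"). The definition sets no threshold for site, severity or action taken.

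Under Interventions, the intervention arm receives "specifically nadroparin 5700 AxaIU administered two times per day" and the control arm "2850 AxaIU once daily for those weighing ≤100 kg, or 5700 AxaIU once daily for those weighing >100 kg". The Discussion restates the contrast: "patients in the intervention group receive nadroparin two times per day, while those in the control group receive it once daily". The Introduction gives the route as one reason for choosing the drug: it "can be administered subcutaneously".

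The Discussion also says that the trial is open label. The blinded trial nurse described under Outcomes makes assessments at the 6-month visit. The article describes no blinded classification of bleeds during admission.

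**The concern.** The class puts a bruise at a puncture site together with a bleed that prompts medical action. The arms differ by design in the number of punctures, so the expected count of local bleeds differs even if each injection carries the same risk in both arms. Because the outcome counts reported bleeds and carers know the allocation, trivial bleeds may also be noted more readily in the high-dose arm.

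The article names safety alongside efficacy as an aim and says the results will inform whether to go on to phase III. With 50 patients per arm, major bleeds may be few, and the non-major class may then carry much of the safety reading. A pooled excess could be taken for systemic harm when it is mainly local. Equally, many trivial events could dilute an excess of the bleeds that matter.

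**Working it through.** The article states no bleeding rate and no power for this outcome, so there is no figure to reproduce. The check asks how large a difference puncture count alone could make.

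**Inputs from the article.** Two v one injection per day (Interventions); median 17 days of high-dose treatment in the retrospective series (Introduction); 21-day maximum (Abstract, Interventions); 50 per arm (Sample size calculation); two-sided 5% level (Statistical analysis).

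**Assumptions.** The per-injection risk q of a reported site bleed is the same in both arms, injections are independent, and q lies between 0.1% and 2%. The article gives no value for q.

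**Injection counts.** Over 17 days: 2 × 17 = 34 v 17. Over 21 days: 2 × 21 = 42 v 21. The ratio is 2 per treatment day to day 21, but the total depends on start and stop. The intervention starts "but no later than 24–72 hours after coiling and will continue for 21 days following the initial SAH", the control arm is treated "starting within 24 hours after coiling and continuing until discharge or when mobilised for at least 6 hours daily", and the intervention arm drops to the prophylactic dose after day 21. Illustrative schedules:
- control stops on day 10, intervention runs to day 17: 34 / 10 = 3.4
- intervention starts on day 4, control on day 1, both to day 17: 28 / 17 = 1.65
- 35-day stay, no stop for mobilisation: (42 + 14) / 35 = 1.6
- the same stay, intervention starts on day 3: (38 + 14) / 35 = 1.49

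The Abstract gives up to 21 days for both arms, whereas Interventions ties the end of control treatment to discharge or mobilisation. These statements need reconciling before exposure can be counted.

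**Incidence of at least one site bleed.** P = 1 − (1 − q)^m, where m is the number of injections.

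**Chance of p<0.05.** Φ[(d − 1.96·SE0)/SE1], where d is the difference in incidence, SE0 the pooled and SE1 the unpooled standard error. At q = 1%, P is 0.2894 v 0.1571, so d = 0.1324 from unrounded values. SE0 = √(2 × 0.223 × 0.777 / 50) = 0.0833 and SE1 = √[(0.2894 × 0.7106 + 0.1571 × 0.8429) / 50] = 0.0822. The argument is (0.1324 − 0.1632) / 0.0822 = −0.375, and Φ = 0.354.

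| q | 34 injections | 17 injections | chance of p<0.05 |
|---|---|---|---|
| 0.1% | 3.3% | 1.7% | 8% |
| 0.5% | 15.7% | 8.2% | 21% |
| 1% | 28.9% | 15.7% | 35% |
| 2% | 49.7% | 29.1% | 56% |

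The normal approximation is poor at 0.1%, where about one or two events per arm are expected (50 × 0.033 = 1.7 and 50 × 0.017 = 0.8). Summing the binomial probabilities of all tables in which the uncorrected χ² test shows an increase gives about 4% there, and 36% and 57% at 1% and 2%.

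**With other bleeds present.** If 20% of patients in each arm have another non-major bleed, P = 1 − 0.8 × (1 − q)^m:
- q = 1%: 43.2% v 32.6%, chance 19%
- q = 2%: 59.7% v 43.3%, chance 38%

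**The case against.** The strongest reply is that the trial compares two regimens. A second daily injection is part of the tested regimen, so the bleeds it causes are a true effect and the randomised comparison stays valid. This stands. A reader might infer that an excess would be spurious, or that the test's false-positive rate rises from 2.5% in that direction to the percentages above. The documents do not support either inference. Under the model the incidences truly differ, so those percentages are power to detect a real difference and the type I error is intact.

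Three further limits stand.
- A reader might take such an excess to be unrelated to systemic risk. That cannot be shown, because dose and frequency change together and greater anticoagulant exposure may itself promote local bleeding.
- At least twice as many injections holds per treatment day to day 21, but not for every patient's total.
- The article never mentions injection-site bleeding, and the case report form is not shown. Bruises may not be recorded as bleeds, and if bleeds cluster in a few susceptible patients the patient-level difference shrinks.

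It can also be said that serious bleeds are already separated, that haemorrhagic complications after shunt placement or lumbar puncture are a separate outcome, and that the article admits limited power. This narrows the problem to the band below major bleeding but does not remove it. Nor is it a detail merely left to an analysis plan: the article itself fixes the definition, and that definition cannot separate the two sources.

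**Conclusion.** The point holds as one of interpretability, not bias. An excess of non-major bleeding, as defined, would be a valid finding about the twice-daily regimen. It would not show whether the excess is systemic or clinically relevant, and the absence of an excess would not exclude a rise in relevant bleeds hidden among trivial ones.

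The size is unknown. It could be negligible if site bleeds are seldom reported (q near 0.1%), or large enough to decide the comparison if q is 1% to 2% and other non-major bleeds are uncommon. All the figures rest on an assumed, equal and independent risk per injection. Any effect of open-label reporting would come on top and cannot be quantified from the article.

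The point is minor to moderate: it concerns one secondary safety outcome. Major bleeding and 30-day mortality are untouched.

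**What to change.** Keep the pooled class as defined and report it. Before the data are analysed:
- Prespecify a clinically relevant non-major category, for example bleeds that prompted medical intervention, a higher level of care or a change of study drug, and make it the main non-major safety comparison.
- Classify it from the bleeds already recorded, by someone unaware of allocation where existing staff allow.
- Tabulate injection-site bleeds separately by arm, as patients affected and per 100 injections given.

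Treatment, sample size and the primary analysis do not change. The cost is a field for site and action taken, and a re-read of bleeds recorded since randomisation began in January 2022. There are two drawbacks. The compared category will hold fewer events, so its interval will be wider. Criteria based on action taken also keep some open-label influence, because the carers who acted knew the allocation; blinded classification reduces this but does not remove it.

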### Sample size calculation

In our retrospective analysis, we found an 18% reduction in mortality when patients were treated with high-dose LMWH (23% mortality in the low-dose LMWH group versus 5% mortality in the high-dose LMWH group, OR 0.19, 95% CI: 0.07 to 0.55).^25^ Although this is a substantial reduction, it was derived from a retrospective, non-randomised design, which limits the ability to assess causal inference and make proper adjustments for confounding prognostic variables. Since we cannot assume this effect size to be accurate without further validation, we aim to conduct a phase II RCT with a total of 100 patients (50 patients per group). After the inclusion and follow-up of these patients, we hope to perform a more reliable power calculation to proceed to a phase III trial.^31^ Besides clinical data, this study will help evaluate the financial and logistical feasibility (including compliance to the study medication, data collection and costs) of establishing a full-scale study.

Each year, 120–125 patients with aSAH are admitted to the Amsterdam UMC, with 80–90 of these patients receiving coiling of the causative aneurysm. Considering the exclusion criteria, we estimate that roughly 25–50 patients per year could be eligible for the ISCHEMIA trial.

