### Statistical analysis

All enrolled patients will be evaluated for the primary and secondary outcomes using an intention-to-treat analysis. To ensure the robustness of the findings, a per-protocol and as-treated analysis will also be conducted, excluding participants who do not complete follow-up, switched treatment groups, had major protocol violations and/or non-adherent patients. Baseline characteristics will be summarised by means of simple descriptive statistics. Continuous data with a parametric distribution will be presented as mean and SD, while non-parametric data will be presented as median and IQR. For between-group comparisons, independent samples t-tests or Mann-Whitney U tests will be used as appropriate. Categorical data will be presented as percentages, with the χ² test used for between-group comparisons.

The treatment effect on the primary outcome (30-day mortality) will be analysed using multivariable logistic regression, adjusting for any clinically relevant baseline imbalances if necessary. Secondary outcomes will be analysed using independent samples t-tests, Mann-Whitney U tests, χ² tests and multivariable linear and logistic regression models, as appropriate. Sensitivity analyses will also be performed, allowing early withdrawal of life support to be considered as a potential confounding variable.

All statistical uncertainty will be expressed using 95% CIs. Statistical analyses will be performed using SPSS (IBM, Armonk, New York, USA), with a significance level set at p<0.05, and all tests will be two-sided.

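### A simple incidence of shunt-dependent hydrocephalus in all enrolled patients is biased against a drug that lowers mortality, and should be shown beside deaths without a shunt

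*Protocol article*

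**What the plan says.** In the protocol article, the Outcomes section states as one secondary objective that the treatment "reduces the incidence of shunt-dependent hydrocephalus, increases the rate of discharge to home". It gives no time point for shunt dependence and does not limit the outcome to survivors.

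The Statistical analysis section sets the population: "All enrolled patients will be evaluated for the primary and secondary outcomes using an intention-to-treat analysis". It sets the methods as follows: "Secondary outcomes will be analysed using independent samples t-tests, Mann-Whitney U tests, χ² tests and multivariable linear and logistic regression models, as appropriate". For a yes/no outcome that means a χ² test or logistic regression. No time-to-event or competing-risk method is named. The one analysis that touches on death is a sensitivity analysis treating early withdrawal of life support as a possible confounder.

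The primary objective is that the drug "significantly reduces mortality assessed at 30 days after the initial bleeding". The Sample size calculation section reports, from the retrospective series, "23% mortality in the low-dose LMWH group versus 5% mortality in the high-dose LMWH group, OR 0.19, 95% CI: 0.07 to 0.55".

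**The concern.** A patient who dies early can no longer become shunt-dependent. If everyone enrolled stays in the denominator and only shunt-dependent patients count as events, a death without a shunt is scored the same as a recovery without one.

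Two courses show the effect. One patient dies in the first week with an external drain and is a non-event. A similar patient survives and later needs a permanent shunt, and is an event. The arm with more survivors has more patients at risk of the event.

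This matters here because the trial's main hypothesis is a difference in mortality. If the hypothesis is true, the shunt comparison is biased against the drug and could mask a benefit or suggest an increase. If the drug raises mortality, the comparison could suggest a benefit that does not exist. The trial is meant to inform a phase III design, so a distorted estimate matters even when it is not significant.

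**Working it through.** **Inputs from the article.** Mortality is 23% (low dose) and 5% (high dose), both retrospective in-hospital figures from the Sample size calculation and Introduction. The Discussion gives an absolute mortality reduction of 5 points as one threshold for moving to a larger trial. There are 50 patients per arm, tested at two-sided 0.05.

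**Assumptions, because the article gives no figures.** Let *s* be the shunt risk in a patient who stays alive, equal in both arms and tried at 10% to 40%. Let *f* be the share of that risk already realised before death in those who die, tried from 0 to 1.

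**The plan's own figure.** 23 − 5 = 18 points. The crude odds ratio is (0.05/0.95)/(0.23/0.77) = 0.176. Rounding of the two percentages allows 0.153 to 0.200, so the stated 0.19 is compatible.

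**Incidence in all enrolled patients.** With mortality *m*, incidence = s(1 − m) + s·f·m. The shunt risk *s* cancels from the ratio between arms.

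- f = 0 (all deaths shunt-free), 23% vs 5%: 0.95/0.77 = 1.23.
- f = 0.25: 0.9625/0.8275 = 1.16.
- f = 0.5: 0.975/0.885 = 1.10.
- f = 1: 1.00.
- f = 0, 23% vs 18%: 0.82/0.77 = 1.06.

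With f = 0 and 23% vs 5%, the gap is 0.18 × s: 1.8 points at s = 10%, 3.6 at 20%, 5.4 at 30% and 7.2 at 40%. That is about 1 to 4 patients per arm of 50. At 23% vs 18% and s = 20% it is 15.4% vs 16.4%, about half a patient.

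**What a true effect would look like (f = 0, 23% vs 5%).** Observed ratio = true ratio × 0.95/0.77.

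- True 0.90 appears as 1.11.
- True 0.80 appears as 0.99.
- True 0.70 appears as 0.86.
- Break-even is 0.77/0.95 = 0.81.

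**Chance of a false signal.** With 50 per arm, f = 0 and 23% vs 5%, a normal approximation gives about a 5% to 11% chance that the artefact alone is significant in the direction of an increase, for s from 10% to 40%. Without any artefact, the chance in that direction would be 2.5%.

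**All three outcomes together (s = 20%, f = 0, no drug effect on shunting).**

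| | Low dose | High dose |
|---|---|---|
| Shunt-dependent | 0.77 × 0.20 = 15.4% | 0.95 × 0.20 = 19.0% |
| Died without a shunt | 23.0% | 5.0% |
| Alive without shunt dependence | 0.77 × 0.80 = 61.6% | 0.95 × 0.80 = 76.0% |

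The first row alone suggests harm. The last row alone suggests benefit, with a ratio of 0.760/0.616 = 1.23. Neither reflects any effect on shunting, and only the full table shows this.

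**Survivors only is not a clean alternative.** Suppose the 18% who are saved have a shunt risk of 40% and the others 20% (assumed). Incidence among survivors is then 20.0% vs (0.77 × 0.20 + 0.18 × 0.40)/0.95 = 23.8%.

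**The case against.** The strongest objection is that the article nowhere says how a death is coded. It gives no definition or time point for shunt dependence and leaves the choice of test open. The full protocol or analysis plan may settle this, and an article commonly leaves such detail to them. This stands in part: the scoring of deaths as non-events is inferred from the stated population and methods. The point is not that detail is missing, though. Taken as stated, an incidence in all enrolled patients tested by χ² or logistic regression has this property.

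Second, the simple incidence in all randomised patients is a legitimate quantity. With complete follow-up it equals the cumulative incidence with death as a competing event, and it keeps the randomised comparison. Mortality is also reported, at 30 days and 6 months. This stands, so the incidence should be kept and not called an error. The risk lies in reading it alone as evidence on the stated objective.

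Third, the size depends on figures that the sponsor declines to rely on. The Sample size calculation says the 18-point difference cannot be taken as accurate, and nothing in the article ties progression to shunt incidence. This also stands, and it limits the weight of the point.

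Fourth, a composite of survival without shunt dependence is itself moved by mortality, as the table shows. It can support the incidence but cannot replace it.

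A reader might infer that a life-saving drug would necessarily appear to increase shunt dependence. The figures do not support that. Even at 23% vs 5% with every death shunt-free, the sign reverses only if the true risk ratio is above about 0.81.

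**Conclusion.** The concern holds as a minor point. As stated, the comparison is biased against a drug that lowers mortality and in favour of one that raises it. With no effect on shunting, the spurious risk ratio is at most 1.23 at 23% vs 5% and about 1.06 at a 5-point reduction. It shrinks towards 1 as more patients are shunted before they die.

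These are upper limits with respect to the timing of deaths, and they assume the same shunt risk in both arms' survivors. If the patients saved had a higher shunt risk (40% against 20%, assumed), the ratio would be 0.226/0.154 = 1.47. The article gives neither shunt rates nor the timing of deaths relative to shunting, and the mortality figures are retrospective stand-ins. The documents do not support saying that the plan expressly scores the dead as successes, or that a false increase is certain.

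**What to change.** Four changes to the analysis wording:

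1. Keep the incidence in all randomised patients, and describe it as the risk of shunt dependence with death as a competing event.
2. Report three exclusive outcomes by arm at 6 months: shunt-dependent, died without a shunt, alive without shunt dependence.
3. Add a comparison of being alive without shunt dependence at 6 months, in all randomised patients, as a supporting analysis.
4. State that no reduction or increase in shunt dependence will be claimed from the simple incidence alone.

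The cost is a few lines of text. Shunt dependence, mortality and a 6-month assessment are already planned, so the only requirement is that shunt status is known to 6 months. The downside is that the supporting outcome is partly driven by mortality, so it must be read with its components and not as a replacement.

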**Methods and analysis:**

This is a single-centre, prospective, phase II randomised controlled trial. From January 2022, all eligible patients will be recruited. 100 patients will be randomised to the intervention arm, that is, nadroparin two times per day 5700 AxaIU, or the control arm, that is, nadroparin once daily 2850 AxaIU in patients with body weight ≤100 kg or once daily 5700 AxaIU in patients with body weight >100 kg, both for up to 21 days. The trial includes a 6-month follow-up period. The primary objective is 30-day mortality rate. Secondary outcomes include assessment of DCI, complications during admission, discharge location, clinical outcome (modified Rankin Scale), quality of life and total healthcare costs at 3 and 6 months follow-up.

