### Allocation and randomisation

After obtaining informed consent, patients will undergo randomisation with stratification for World Federation of Neurosurgical Societies (WFNS) score. Five strata were defined, one for each WFNS score. Within each stratum, separate randomisations are performed between the intervention and control group to ensure a balanced randomisation based on disease severity. This is particularly important because, in patients with high-grade WFNS scores, goals of care may shift toward comfort-focused measures, which can independently affect mortality outcomes regardless of the intervention. Stratification by WFNS grade helps mitigate this potential source of bias. Randomisation is conducted using a web-based permuted block system and performed by the principal investigator or executive researcher. This system employs permuted blocks of variable sizes, ranging from two to six patients, to minimise the predictability of group allocation and ensure balanced sample sizes in each study arm. Patients are randomised in a 1:1 ratio and assigned to one of the two treatment arms.

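### The 6-month functional objective is worded as a yes/no outcome although the modified Rankin Scale is collected; an ordinal analysis adjusted for WFNS grade should be named as the main one

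*Protocol article*

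**What the plan says.** Three places in the protocol article bear on the 6-month functional outcome.

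- **Abstract, Methods and analysis.** The secondary outcomes include "clinical outcome (modified Rankin Scale), quality of life and total healthcare costs at 3 and 6 months follow-up". The scale is named and no dichotomy is mentioned.
- **Outcomes.** The matching objective is whether treatment "increases the likelihood of a favourable outcome at 6 months". Neither a scale nor a cut-off is attached. The same list defines major and non-major bleeding and names the scale for DCI severity.
- **Statistical analysis.** "Secondary outcomes will be analysed using independent samples t-tests, Mann-Whitney U tests, χ² tests and multivariable linear and logistic regression models, as appropriate". No method is tied to the mRS, and ordinal regression is not named.

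Two design facts matter for the check. Randomisation is stratified by WFNS score in five strata (Allocation and randomisation), and the planned size is 50 patients per group (Sample size calculation).

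**The concern.** The abstract names a seven-level scale and the objective names a yes/no event. The statistical section does not say which of the two will be analysed. An analysis that follows the objective literally would split the mRS at one point and ignore movement between levels on either side of it. In a trial of 100 patients that loss is not trivial.

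The choice of adjusted model has the same effect. The multivariable models listed are linear and logistic. An adjusted mRS analysis drawn from that list would therefore either treat the scale as an interval measure or cut it. The rank test on the list uses all levels but cannot adjust for WFNS grade, the factor on which patients were stratified. As usually reported, it also gives no odds ratio with a confidence interval, although the section promises 95% CIs throughout.

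At stake are the precision of a functional comparison that the trial already pays to collect, and its usefulness as an estimate to carry forward.

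**Working it through.** **The plan's own figure.** None exists to reproduce. The article gives no power for the mRS, and the total of 100 is not derived from a power target.

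**Inputs from the article.** 50 per arm; 1:1 ("Patients are randomised in a 1:1 ratio and assigned to one of the two treatment arms"); "with a significance level set at p<0.05, and all tests will be two-sided".

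**Assumed inputs.** The article gives no mRS distribution, so four control distributions (percent in mRS 0 to 6) were assumed, with a common odds ratio (OR) at every cut:

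- A: 15/25/20/12/8/5/15 (mRS 0–2 in 60%)
- B: 10/18/18/15/12/7/20 (46%)
- C: 6/12/14/14/14/10/30 (32%)
- D: 10/15/17/15/12/8/23 (42%)

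**Formulas.**

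- Treated arm: at each cut, treated odds = OR × control odds.
- Full scale (Whitehead, proportional odds): V = (N/12)(1 − Σ p̄³), where p̄ is the mean of the two arms' proportions at each level; power = Φ(ln OR × √V − 1.960).
- Single cut: power = Φ((|p₁ − p₂| − 1.960 × se₀)/se₁), with se₀ = √(p̄(1 − p̄) × 2/50) and se₁ = √((p₁(1 − p₁) + p₂(1 − p₂))/50).

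**Worked case: distribution A, OR 2.**

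- Full scale: Σ p̄³ = 0.0405, so V = (100/12)(0.9595) = 7.996 and √V = 2.828. Then 0.6931 × 2.828 = 1.960, and power = Φ(1.960 − 1.960) = 50%.
- Cut 0–2: 0.60 has odds 1.5, doubled to 3.0, so the treated proportion is 0.75. p̄ = 0.675, se₀ = 0.0937, se₁ = 0.0925. (0.15 − 1.960 × 0.0937)/0.0925 = −0.363, and power = 36%.
- Cut 0–3: 0.72 has odds 2.571, doubled to 5.143, so the treated proportion is 0.837. se₀ = 0.0830, se₁ = 0.0822. (0.117 − 0.163)/0.0822 ≈ −0.55, and power = 29%.

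**Results at OR 2, 50 per arm.**

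| Control distribution | Full scale, formula | Mann-Whitney, simulated | Cut 0–2 | Cut 0–3 |
|---|---|---|---|---|
| A | 50% | 49% | 36% | 29% |
| B | 51% | 49% | 40% | 35% |
| C | 51% | 50% | 39% | 40% |
| D | – | about 50% | 43% | 37% |

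For A to C the cuts use the formula and the rank test was simulated with 4,000 runs. For D both the rank test and the Pearson chi-square were simulated with 10,000 runs. The formula puts D's cut 0–2 at 40% (0.42 to 0.59). The 43% is the simulated value and is kept as the upper end of the range.

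The loss from a single cut is 7 points (50 − 43, D) to 21 points (50 − 29, A).

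**Other effect sizes (A to C).**

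| Common OR | Full scale | Single cut |
|---|---|---|
| 1.5 | 21% | 14–17% |
| 2.5 | 74% | 43–61% |
| 3.0 | 87–88% | 55–77% |

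For 80% power at OR 2, the total is 202–205 patients on the full scale and 268–392 with a cut. The ratio is 268/202 = 1.3 to 392/205 = 1.9.

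The choice of cut matters too. In distribution A at OR 3, power is 68% for cut 0–2 and 55% for cut 0–3.

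All these figures are unadjusted. Any gain from adding WFNS grade was not quantified.

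**The case against.** The case on the other side is substantial, and most of it stands.

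- **No text says the scale is collapsed.** A reader might infer that the mRS will be reduced to a dichotomy and the rest thrown away. The Outcomes section states an objective, does not mention the mRS there and fixes no analysis. That the favourable outcome is a cut of the mRS is a sensible inference only.
- **A full-scale test is already listed.** Mann-Whitney has almost the same power as the proportional-odds model in these scenarios. What it lacks is adjustment for WFNS grade and an odds ratio with a CI.
- **The cut-off may be defined elsewhere.** This is a journal article. The full protocol and SAP are not shown and commonly hold such definitions, so the absence here is not a finding. For the same reason, the worry that a cut could be picked after results are seen cannot be established. Blinding of the 6-month assessor protects the scoring, though not the choice of cut.
- **The mRS has no stated role in designing phase III.** The only progression threshold, in the Discussion, is on mortality: a 5% absolute or at least 20% relative reduction.
- **The retrospective data do not size the loss.** Combining discharge home (40% vs 17%) with in-hospital death (5% vs 23%) as three ordered levels gives simulated power of 91%, against 74% for home yes/no. Those are in-hospital death and discharge destination, not 6-month mRS. The article itself says the mortality effect cannot be assumed accurate.
- **A mid-scale cut still registers deaths**, as unfavourable, and 6-month mortality is a separate outcome.
- **The outcome is secondary, and the article concedes low power** for mortality and other parameters.

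The objection does not remove the mismatch between a binary objective and a named scale, or the lack of any listed model that both uses the full ordinal scale and adjusts for the strata.

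**Conclusion.** The point holds as a modest improvement to a secondary analysis. The objective is worded as binary, the abstract names the scale, and the statistical section does not connect them. If the objective is analysed as worded, the cost at a common odds ratio of 2 is about 7 to 21 power points out of about 50.

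That size rests on assumed control distributions, on exact proportional odds (which favours the full-scale method) and on reading the favourable outcome as a cut of the mRS. The full-scale analysis was ahead in every scenario tested, but at an odds ratio of 2 neither approach is well powered with 100 patients. The benefit is better use of the data. It would not make the functional comparison definitive.

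**What to change.** In Statistical analysis, name the main 6-month functional analysis: proportional-odds logistic regression of mRS 0–6, with death scored 6, on treatment and WFNS grade. Report the common odds ratio with 95% CI and show the mRS distribution by arm. In Outcomes, tie the favourable outcome to the mRS, state one cut-off and label that dichotomy supportive. If the full protocol or SAP already defines it, repeat the definition or refer to it. Settle this before outcomes by arm are seen.

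The cost is wording only: no new data, visits or patients, and SPSS, the planned software, has ordinal regression. The one downside is reliance on roughly proportional odds. The distribution by arm lets readers judge that, and the supportive dichotomy gives a result that does not depend on it.
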